### Recruitment

In the local (Pashtun) culture, it is not possible to directly contact a potential female study participant without prior consent from the husband/male head of the household. Therefore, at each study site, an initial information session was held with the male parents/guardians with the help of elected local representatives and elders of the community. During the session, complete information about the study objectives, eligibility criteria, and data collection process was presented and explained by the team leader in the local (Pashto) language. A participant information sheet containing all the study details and procedures in an easy-to-understand, local (Pashto), and Urdu (national language of Pakistan) were also provided to the parents during the session. All queries were also answered. Following the session, eligible parents/guardians were invited by trained research assistants to enroll their babies in the study. Once they agreed, the parents were asked to sign a written informed consent form in their preferred language.

### Participants, funder and public involvement

Community members, funder (NIH Pakistan) or the participants’ parents were not directly involved in developing the study design, conduct, and outcome measures. The study protocol was reviewed and approved by the Office of Research, Innovation, and Commercialization (ORIC) Khyber Medical University and National Institute of Health (NIH), Pakistan. Healthcare professionals (LHWs) involved in the study had close liaison with the community and acted as a bridge between the researchers and participants. They also contributed to the design of the data collection questionnaires, informed consent, and helped ensure confidentiality. However, the individual data were not reported to the participants.

### Study procedures

Figure 1 provides an overview of the overall study flow.

**Figure 1. f1:**
[figure not shown]
Flowchart of the study.

### Data collection

We will collect different data from both mother and infant at baseline and at each time point during the follow-up period. The data collection in this project used an Android version of the KoBoCollect/Toolbox as a data collection instrument. To collect the demographic and socioeconomic information of the study participants, an interviewer administered a structured questionnaire will be used. The questionnaire included information such as name, age, sex, household information, and socioeconomic status. Details about ante-natal and post-natal care will also be recorded using a structured, validated questionnaire adapted from the National Nutrition Survey Pakistan questionnaire.
^
34
^ Sociodemographic, ante-natal and post-natal care data will be recorded only at baseline, that is, at the start of the study.

The Dietary Quality Questionnaire (DQQ) will be used to assess the dietary intake of mothers. This method was chosen because, in Pakistan, there is no validated food frequency questionnaire to assess dietary intake. The DQQ is a standardized and easy-to-use tool to collect food group consumption data required for calculating diet quality indicators, such as Minimum Dietary Diversity for Women (MDD-W). The questionnaire has been validated and implemented across more than 100 countries including Pakistan.
^
35
^ The DQQ is a list-based method consisting of yes/no responses to 29 food groups consumed by the respondent during the previous day and night (24 hours). The procedure typically requires approximately 5–7 minutes to complete. Information regarding feeding practices of the children will be collected using validated, semi-structured questionnaires based on Infant and Young Child Feeding Practices (IYCF) indicators developed by the Technical Expert Advisory Group on Nutrition Monitoring (TEAM) of the WHO.
^
36
^ This set of simple, validated, and reliable indicators is widely used to assess IYCF practices across the globe, especially in low- and middle-income countries. The IYCF indicators were assessed by interviewing the mothers or the main caregivers. The mothers will also be interviewed to collect data about the child’s medical history, diarrhea and respiratory tract infection, hospitalization, and use of antibiotics using a structured questionnaire. DQQ, IYCF, and child health record data will be collected at baseline and at each time point during follow-up.

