## Abstract

Recent evidence suggests that the development of gut microbiota during infancy affects several metabolic, immune, and endocrine pathways in humans. An imbalance in gut microbiota diversity or function, also known as dysbiosis, not only affects early child growth and development, but is also linked with the development of chronic, non-communicable diseases in later life. The
**C**hild
**H**ealth
**A**nd
**M**icrobiome Development Study –
**P**akistan (CHAMP) study aimed to longitudinally assess gut microbiota development and associated factors (maternal, child, and demographic) during early childhood in populations residing in malnutrition-endemic communities in Pakistan. A prospective cohort of mother-infant pairs (n=70) will be recruited from District Swat, Pakistan, and followed for two years. Complete information about demographic characteristics, anti-natal and post-natal care, dietary intake, feeding practices, and child health will be collected at baseline and 3, 6, 12, 18, and 24 months. Anthropometric measurements (height, weight, mid-upper arm circumference, and head circumference), dry blood spots, and fecal samples were also collected. Ethical approval for the study was obtained from Khyber Medical University, Pakistan. The study is also registered on
clincaltrial.gov (Ref no: NCT05793294). The study findings will help researchers understand gut microbiota development, associated factors, and their impact on longitudinal growth in infants during the first two years of life.

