## Introduction

Infancy, the period from birth to around two years of age, is a crucial stage in human development, characterized primarily by rapid physical, mental, and emotional growth.
^
1
^ During this period, many environmental factors such as gestational age, sex, ethnicity, dietary intake, nutritional status, and socioeconomic conditions significantly affect child growth, development, and overall health.
^
2,
3
^ However, to date, these factors, either alone or synergistically, have failed to explain the overall spectrum and variations in children. Recent studies have emphasized that apart from the intersection of environmental factors, the gut microbiome also plays an important role in mediating growth and development, especially during infancy.

The human fetus is believed to develop in a microbe-free environment.
^
4
^ However, immediately after birth, the infant gut, especially the distal ileum and colon, is rapidly colonized by different microorganisms (bacteria, fungi, archaea, and viruses) via vertical transmission from maternal body sites such as the vagina, skin, oral cavity, and gut.
^
5
^ In newborn infants, the gut microbiota exhibits low diversity, consisting mainly of facultative anaerobic bacteria, such as
*Proteobacteria* (e.g.,
*Escherichia* and
*Enterobacter*) and
*Firmicutes* (
*Staphylococcus*,
*Enterococcus*and, and
*Streptococcus*).
^
6
^ Early colonization has a profound influence on the gut environment and subsequent colonization by obligate anaerobes, such as
*Bifidobacterium, Bacteroides* and
*Clostridium.* The relative abundance of
*Bifidobacteria* gradually increases 3 – 4 days after birth and becomes a predominant bacterial genus when the baby is approximately 1 month old.
^
7,
8
^ In healthy growing children, the gut microbiota gradually increases in complexity with a highly diverse microbial composition during and after the first two–three years of life.
^
9
^ During this period, the patterned ecological assembly of microbes occurs mainly under the influence of delivery mode, type of feeding, complimentary feeding practices, antibiotic use, and geography.
^
9–
12
^ Gut microbiota development during early life affects several metabolic, immune, and endocrine pathways and is thus intimately linked to child growth and development.
^
13

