## Protocol

### Objectives

The primary objective of the CHAMP study is to characterize gut microbiota development and longitudinal growth in infants during the first two years of life. This will be done by assessing the microbial diversity, relative abundance of the dominant microbiota, and interindividual variations in microbial diversity and infant growth patterns. The secondary objective of the study is to investigate the impact of (i) sociodemographic characteristics, (ii) mode of delivery, (iii) maternal factors such as diet and anti-natal and post-natal care, (iv) child dietary intake and feeding practices, and (v) nutritional status of the child on gut microbiota composition at different time points from birth until the child is two years old.

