### Participants selection

The study population will include 70 mother-infant pairs (dyads), according to the following criteria:

Inclusion criteria
•Apparently healthy infants of both genders aged 0 – 28 days•Born by natural or caesarean delivery•Born to parents from district Swat•Parents/caregivers have no plans to move out of the stud site for at least two years after enrollment in the study.

The exclusion criteria are:
•Child born to an underage (<18 years old) mother.•Infants born with severe acute or chronic medical conditions that require hospitalization, prolonged use of medication, or both, or diagnosed with enteropathies.•Weight of the child is <1500 gm.

Ethical approval for the study was granted by the Research Ethics Board of Khyber Medical University. This study was also registered at
www.clinicaltrial.gov (NCT05793294).

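### Post-natal care is scheduled for baseline only in one place and for every visit in another; if recorded only at baseline (age 0 to 28 days), the exposure is liable to age-dependent misclassification

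*Protocol article*

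**What the plan says.** The protocol article gives two schedules for the same item. Data collection: "Sociodemographic, ante-natal and post-natal care data will be recorded only at baseline, that is, at the start of the study". The same section then names what is repeated at follow-up (the maternal diet questionnaire, the infant feeding indicators and the child health record). Post-natal care is not among these. The abstract instead lists: "anti-natal and post-natal care, dietary intake, feeding practices, and child health will be collected at baseline and 3, 6, 12, 18, and 24 months".

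Three other statements bear on the point:

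- Participants selection admits "Apparently healthy infants of both genders aged 0 – 28 days".
- Objectives (secondary) includes "maternal factors such as diet and anti-natal and post-natal care" among the factors whose impact is studied "on gut microbiota composition at different time points from birth until the child is two years old".
- The Introduction describes marked change within the first month; the share of Bifidobacteria, it says, "gradually increases 3 – 4 days after birth and becomes a predominant bacterial genus when the baby is approximately 1 month old".

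**The concern.** Ante-natal care is complete at birth, so one baseline question can capture it. Post-natal care is still accruing during the enrolment window. Under the Data collection schedule, a mother seen in the first days has had little time to receive any, while one seen on day 28 has had four weeks. A recorded no can mean either that no care was received or that none had been received yet, and care after the visit is never captured.

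Two consequences are at stake:

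- Counting later care as none pulls a true association with the microbiota towards zero, at every visit.
- In the baseline stool samples, infant age influences both the chance of recorded care and the microbiota, so a comparison that ignores age can show an association that care did not cause.

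**Working it through.** The plan states no figure to reproduce. The check sets the schedules side by side and then illustrates the size.

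**Schedules.** Abstract: post-natal care at baseline and at 3, 6, 12, 18 and 24 months. Data collection: baseline only. Both cannot hold. The child health record is repeated, but it covers medical history, diarrhoea, respiratory infection, hospitalization and antibiotics. It does not replace post-natal care.

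**Inputs.** From the article: enrolment age A between 0 and 28 days; n = 70. Assumed, because the article does not give them: A uniform on 0 to 28 days, baseline visit at enrolment, and a look-back window W of 2, 7, 28 or 42 days from birth.

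**Share of the window visible at baseline.** This is the mean of min(A, W)/W. For W up to 28 it equals 1 − W/56; for W of 28 or more it equals 14/W.

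- W = 2: 1 − 2/56 = 0.964
- W = 7: 1 − 7/56 = 0.875
- W = 28: 1 − 28/56 = 0.50
- W = 42: 14/42 = 0.333 (7/42 = 0.17 for an infant seen on day 7; 28/42 = 0.67 on day 28)

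The window is still open at baseline for 2/28 = 7% of infants if W = 2, for 7/28 = 25% if W = 7, and for essentially all if W is 28 or 42.

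**Attenuation.** Assume further that 60% of mothers truly have a contact, at a time uniform over W, recorded only if it precedes baseline. The visible share s is then the sensitivity of the baseline record. A true difference d shrinks to d × 0.4/(1 − 0.6s), because the recorded-no group contains mothers who later had care. For d = 0.5 SD:

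- s = 0.964: 0.5 × 0.4/0.4216 = 0.47
- s = 0.875: 0.5 × 0.4/0.475 = 0.42
- s = 0.50: 0.5 × 0.4/0.70 = 0.29
- s = 0.333: 0.5 × 0.4/0.80 = 0.25

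**False association at baseline.** Assume no effect of care and an outcome that rises by 1 SD over the 28 days. For W of 28 or more, recorded care is proportional to age, so the mean age of recorded users is (28²/3)/14 = 18.7 days.

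- W = 28: 30% are recorded users; the others average (14 − 0.3 × 18.67)/0.7 = 12.0 days. The gap is 6.7 days, or 6.7/28 = 0.24 SD.
- W = 42: 20% are recorded users; the others average (14 − 0.2 × 18.67)/0.8 = 12.8 days. The gap is 5.8 days, or 0.21 SD.

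**Simulation under the same assumptions (n = 70, 3,000 replicates per setting).**

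| W (days) | Estimate, true 0.5 SD, no age trend | Same, age-adjusted | Estimate, true 0, age trend 1 SD | Wilcoxon rejection at nominal 5% | True 0, age-adjusted |
|---|---|---|---|---|---|
| 2 | 0.47 | 0.47 | 0.05 | 5% | 0.00 |
| 7 | 0.42 | 0.44 | 0.13 | 7% | 0.01 |
| 28 | 0.28 | 0.32 | 0.23 | 13% | −0.01 |
| 42 | 0.25 | 0.27 | 0.21 | 10% | 0.00 |

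The simulation agrees with the formulas. Age adjustment removes the false association but leaves most of the attenuation.

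**The case against.** **The conflict may be only loose wording in the abstract.** The abstract puts all data domains into one sentence and schedules even demographic characteristics for every visit, whereas Data collection is explicit. That is fair, and the body text is probably the intended schedule. But the truncation arises under exactly that schedule, so correcting the abstract alone does not remove it.

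**A reader might infer that the post-natal care association is biased, and heavily so.** For example, with a 42-day window, a constant contact rate and 30%, 50% or 70% of mothers ever receiving care, baseline would record care in 11.0%, 19.9% or 31.2% of all mothers. That is 37%, 40% or 45% of those who receive it. The documents do not support this as a finding. The window, contact rate and distribution of enrolment ages are not given, and the questionnaire is deposited separately and not shown. If it asks only about the first days after birth, little is lost. Care concentrated soon after birth would also raise capture. So would later enrolment, which is plausible given the register, health-worker, guardian-session and consent steps.

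**A reader might also infer that the false baseline association cannot be avoided.** It can: date of birth is recorded, so age at sampling is known and can be adjusted for. Data analysis states no such adjustment, but an analysis plan may, and its absence from an article is not an error. The attenuation remains.

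**Weight.** Post-natal care is one example within one of five secondary exposure groups, and Data analysis does not name it among the metadata to be related to the microbiota. This limits the consequence.

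**Late recall.** By October 2024, 66 of 70 dyads had reached the 3-month visit, so a new question would mean recall over months. This stands, and is a reason to supplement the baseline answer and not discard it.

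**Conclusion.** The point holds in a conditional form. The two schedules contradict each other. If the Data collection schedule is followed, the post-natal care exposure is liable to misclassification that depends on age at enrolment. With enrolment age uniform on 0 to 28 days, the average loss ranges from about 4% of a 2-day window to 67% of a 42-day window. Under the further assumptions above, a true 0.5 SD difference would appear as 0.47 SD at the short end and 0.25 SD at the long end. An age trend of 1 SD could produce a false unadjusted baseline difference of about 0.05 to 0.23 SD. The existence of the truncation follows from the article; its size does not. It should be corrected, because for a long window analysis alone cannot recover care that was never recorded. It concerns one secondary exposure and leaves the primary objective untouched.

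**What to change.** 1. Reconcile the abstract with Data collection, and state the look-back window of the post-natal care questions.
2. Keep the baseline answer. Repeat the post-natal care block once, at each dyad's next scheduled visit, over one fixed window counted from birth that has closed for every child when asked.
3. Define the exposure over that window from both answers together, and report a sensitivity analysis using the baseline answer alone.
4. Adjust comparisons of the baseline samples for infant age in days at sampling. ADONIS can take age as a covariate. The Wilcoxon test cannot, so alpha diversity needs a regression model for this exposure.
5. Leave ante-natal care at baseline only.

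Cost: a few minutes at one visit that is already planned, within follow-up that runs to May 2026. The downside is recall over several months for the dyads already past the 3-month visit, in a study that already lists retrospective self-report as a limitation; the sensitivity analysis addresses this. If the stated look-back covers only the first days after birth, the repeat matters only for the few infants seen before it closed.

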### Anthropometric assessment

At baseline and at each time point, the following anthropometric assessment will be performed on each child/infant and their mothers using standard methods.
^
37
^

**Height/length:** Recumbent length will be measured using an infantometer. Before measuring, the measuring board will be placed on a hard, flat surface such as a ground or sturdy table. The mother will be asked to place the child gently on the board such that the infant’s head is aligned against the headboard while an assistant straightens the infant body and feet. When the child is position is correct, the researcher moves the foot board firmly against the child’s heels. The length of the child will be recorded to the nearest 0.1 cm. The measurement will be repeated twice, and the average of the two measurements is recorded as the final length of the child. Mothers’ height will be recorded using a stadiometer following standard protocols. Briefly, they will be asked to remove shoes and gently stand on stadiometer. To ensure accurate measurement, the mothers will be instructed to stand up against the board, ensuring the Frankfurt plan position in which the back of the head, shoulder blades and buttocks and heels touch the back of the stadiometer. Once ready, the researcher will gently and firmly slide the measuring board’s moveable headpiece down until it touches the crown of the person’s head (compresses the hair). The procedure is repeated twice and the average of the two measurements is recorded as the height of the mother.

**Weight:** To record the weight of the child, a specialized electronic scale (Secca, UK) will be used. Before weighing the child, the parent will be instructed/helped to remove shoes, socks and heavy clothing except dry clean diapers or underpants from the child. When ready, the child is placed on his/her back on the center of the scale pan with the help of a trained researcher. We wait until the infant is still in the pan and the digital display is no more changing. The weight of the child will be recorded to the nearest 0.01 kg. The weight of the mother is measured in kilograms using a calibrated electronic weighing scale. The mothers will be asked to remove shoes, jewellery and extra clothing (dupatta/chaddar) and stand calmly on the scale. The weight will be recorded to the nearest 0.01 kg twice and the average of the two measurement is considered the final weight of the mother.

**Mid upper arm circumference (MUAC):** For infant MUAC measurements, a non-stretchable, numbered and colored MUAC tape will be used. To prepare for the measurement, the infant mother will be asked to sit on a comfortable chair, place the child in her lap and remove any clothing covering the left hand of the child. The mid-point between the tip of the elbow and the shoulder is located by straightening the arm along the axis of the body and forearm at 90-degree forwards. Once the mid-point is marked with a pen, the arm is straightened and the MUAC tape is placed around the arm at the midpoint and the reading is taken to the nearest mm.

**Head circumference:** The head circumference of the child will be measured using a non-stretchable measuring tape around the most prominent part of head to the middle of the forehead while the hair and soft tissue is compressed. At least two measurements will be recorded and the average of the two will be taken.

### Sample collection

**Dry blood spot:** Dry blood spots (DBS) are collected from both the mother and the infant at baseline and during the follow-up by skin puncture of the third or fourth finger of the non-writing hand.
^
38
^ Before DBS collection, the participants’ hands are first warmed, followed by anterograde massaging of the finger in the direction of blood flow towards the puncture site. The DBS collection site, that is, the palmar side of the tip of the distal phalanx, is cleaned with 70% isopropyl alcohol and punctured using a single-use lancet. The first drop of blood is wiped off with a gauze pad, and subsequent drops were transferred to the marked circles on the surface of the filter paper without touching the surface. After drying, the DBS papers will be transferred to a zip-lock bag and stored at -80 °C until further processing in the KMU main lab.

**Stool:** Stool samples are collected from the diapers of infants at each time point. For this purpose, the parents will be provided diapers, a specimen collection jar, disposable gloves, a zip lock bag, and an instruction sheet one day before sample collection. The parents are instructed to regularly check their child’s diaper and remove it immediately after the child passed the stool. Stool samples are transferred immediately to the specimen container, placed in a zip-lock bag, and handed over to the research assistant within 4 h of sample collection. The research assistant transferred 400 mg of stool sample into 2 mL screw-top tubes prefilled with DNA shield reagent (Zymo Research USA) and sent it to the main KMU lab at room temperature, where it will be stored at -80 °C.

### Laboratory analysis

**Hematological assessment**

Dry blood samples will be used to assess the biomarkers of infections, micronutrient deficiencies, and inflammation. For this purpose, commercially available chemiluminscence-based Q-plex Aray kits (Quansys Biosciences) will be used following the manufacturer’s instructions. This assay reliably detects and quantifies histidine-rich protein II (biomarker of malarial infections), C-reactive protein, alpha-1-acid glycoprotein (biomarkers of inflammation), ferritin and soluble transferrin receptor (biomarker of iron deficiency), retinol binding protein (biomarker of vitamin A deficiency), and thyroglobulin (biomarker of iodine deficiency).
^
39
^

